### Primary Outcome

The primary outcome upon which the trial is powered is the difference between groups in the change in HbA_1c_ from baseline to 12 months. HbA_1c_ was chosen for several reasons: it is the principal clinical measure of diabetes status and glycemic control, and a valuable surrogate measure of holistic engagement with diabetes management and self-care; reduction of HbA_1c_ is associated with reduced risk of micro and macrovascular complications, and in some cases, all-cause mortality [45]; it is also a prominent component of the Core Outcome Measures in Effectiveness Trials initiative core outcomes set for T2D [46]. A 12-month primary endpoint has been chosen to examine the effectiveness of the HEAL-D intervention, as this is a duration long enough to observe a clinically important difference in HbA_1c_.

### Secondary and Exploratory Outcomes

At 6 and 24 months, HbA_1c_ will be measured as a secondary outcome to allow exploration of the time-course of any observed changes and impact of HEAL-D over a longer period. Other secondary outcomes (Table 1), measured at 6, 12, and 24 months, are grouped into holistic health domains and include cardiovascular risk factors, psychological well-being and self-management support, lifestyle behaviors, and health economics.

Tertiary outcomes are low-density lipoprotein-cholesterol, triglycerides, body fat percentage, changes to glucose-lowering and antihypertensive therapies (including addition, removal, or dose adjustment), and changes in MLTC status (including additional diagnoses, remission, or changes in severity).

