### Aims

The primary aim of this trial is to evaluate the effectiveness of the HEAL-D intervention, compared to standard DSMES programs, on glycemic control (assessed via HbA_1c_) at 12 months in Black African and Black Caribbean adults living with T2D. It is hypothesized that the HEAL-D intervention will improve glycemic control to a greater extent than standard DSMES programs at 12-month follow-up. Secondary aims include testing the effectiveness of HEAL-D, compared to standard DSMES programs, on cardiovascular risk factors; psychological well-being and QoL; T2D knowledge and self-efficacy; and diet and physical activity behaviors at 6, 12, and 24 months, as well as assessing cost-effectiveness. A mixed methods process evaluation aims to assess HEAL-D delivery, intervention fidelity and implementation, and the impact of multiple long-term conditions (MLTC) on recruitment and engagement with the HEAL-D intervention, and the impact of HEAL-D on MLTC.

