## Methods

### Study Design

The trial is a 24-month, multicenter, pragmatic, open-label, 2-arm, parallel-group, individually randomized group treatment trial assessing the clinical and cost effectiveness of the HEAL-D program compared with standard DSMES programs in Black African and Black Caribbean adults living with T2D. A total of 300 Black African and Black Caribbean adults living with T2D will be recruited and randomly allocated to either the HEAL-D program (n=150) or a standard DSMES program (control, n=150). Outcome assessments will be conducted at baseline and 6, 12, and 24 months after randomization (Figure 1). Embedded within the trial are an internal feasibility assessment of recruitment, allocation and intervention engagement; a health economic analysis; a mixed methods process evaluation of intervention delivery, fidelity, implementation and acceptability; and study within a project (SWAP) to assess the impact of MLTC on the uptake of and engagement with HEAL-D, and the impact of the intervention on MLTC.

The trial is funded by the National Institute for Health Research (NIHR) Health Technology Assessment Program (NIHR151372) and is registered with ISRCTN (14344948), which adheres to the World Health Organization (WHO) Trial Registration Dataset. Health Research Authority and Research Ethics Council approval was received on April 22, 2024.

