**Tertiary or exploratory outcomes**						
	Blood lipids					
		LDL^k^-cholesterol (mmol/L); nonfasting blood sample	✓	✓	✓	✓
		Triglyceride (mmol/L); nonfasting blood sample	✓	✓	✓	✓
	Body composition: body fat (kg and %); measured using bioelectrical impedance analysis		✓	✓	✓	✓
	Lifestyle behaviors: self-reported sleep duration and chronotype		✓	✓	✓	✓
	Medication use					
		Glucose-lowering therapies use, assessed via self-reported medication history	✓	✓	✓	✓
		Blood pressure-lowering therapies use, assessed via self-reported medication history	✓	✓	✓	✓
	Multimorbidity status					
		Diagnoses or remission or changes in severity of medical conditions, assessed via self-reported medical history	✓	✓	✓	✓
		MTBQ^l^	✓	✓	✓	✓

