### Statistical Analysis

Primary analysis of change in HbA_1c_ at 12 months will be conducted using a mixed effects model with a random effect for the group attended; individuals in the control arm will be treated as groups of size 1 [64]. Treatment arm, center, and baseline HbA_1c_ will be included as fixed effects. The primary analysis will be repeated to include an interaction term between treatment and mode of delivery (F2F or remote) to explore any differential treatment effect among groups. The presence of an interaction will be tested using a likelihood ratio test. The prespecified subgroup analyses of the primary outcome will assess whether the effectiveness of the intervention is dependent on baseline HbA_1c_ or center. This will be assessed by adding interaction terms between group allocation and the potential effect modifiers to the linear regression, one at a time. The analysis exploring the change in treatment effect over time for the secondary outcomes will follow the methodology of the primary analysis, with an additional random effect for the individual to account for within-individual correlation over time, a fixed effect for time, and an interaction between treatment and time effect. Mediation analysis will be conducted using multilevel structural equation modeling [65]. To account for missing data, multiple imputation will be undertaken, provided we have strong predictors of missingness and an appropriate imputation model. Diagnostic checks will be performed to assess this. The missing data mechanism will be assumed to be missing at random. Individual analyses on each imputed dataset will be combined using the Rubin rules. Sensitivity analyses will be conducted to assess the robustness of the primary conclusions to the imputation strategy used.

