## Discussion

### Overview

The HEAL-D trial will evaluate if a culturally tailored DSMES program, provided in person or remotely, via videoconferencing, is clinically and cost-effective, in comparison with standard DSMES programs, at improving glycemic control (HbA_1c_) at 12-month follow-up in adults of Black African and Black Caribbean ethnicity living with T2D. It is hypothesized that the provision of a DSMES program that is sensitive to the cultural health beliefs and practices of adults of African and Caribbean heritage will promote clinically meaningful improvements in T2D self-management.

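### The 12-month HbA1c comparison is valid whatever drugs are later prescribed, but it cannot alone be credited to self-management, and the primary model leaves collected baseline therapy unused

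*Protocol article*

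**What the plan says.** The Study Design section sets the frame: "The trial is a 24-month, multicenter, pragmatic, open-label, 2-arm, parallel-group, individually randomized group treatment trial". The primary aim is "to evaluate the effectiveness of the HEAL-D intervention, compared to standard DSMES programs, on glycemic control", and the primary outcome is "the difference between groups in the change in HbA_1c_ from baseline to 12 months". For the primary model, the Statistical Analysis section says "Treatment arm, center, and baseline HbA_1c_ will be included as fixed effects", with a random effect for the group attended. Randomization is stratified by center and baseline HbA1c band. Baseline therapy is in neither list, although Table 1 collects medication history at baseline.

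Drug change is placed elsewhere. The Secondary and Exploratory Outcomes section names as tertiary "changes to glucose-lowering and antihypertensive therapies (including addition, removal, or dose adjustment"). Table 1 gives the source as "Glucose-lowering therapies use, assessed via self-reported medication history", at baseline and at 6, 12 and 24 months. The article neither restricts glucose-lowering therapy during follow-up nor says how a change before month 12 bears on the primary effect.

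Two statements give HbA1c a behavioral meaning. The Primary Outcome section justifies it partly as "a valuable surrogate measure of holistic engagement with diabetes management and self-care". The Discussion overview, directly after naming glycemic control as the question, hypothesizes that a culturally sensitive program "will promote clinically meaningful improvements in T2D self-management".

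**The concern.** Glucose-lowering drugs act directly on HbA1c. Over 12 months of usual care, a participant whose HbA1c stays high may have treatment intensified, and one who improves may have it reduced. If the first happens more in the control arm and the second more in the HEAL-D arm, the arms draw together. If contact with the HEAL-D dietitian prompts more medication review, they draw apart. The documents do not settle the direction.

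What is at stake is the explanation attached to the result. A small HbA1c difference could conceal equal control reached with less drug. A large one could be partly a prescribing effect. HbA1c alone cannot tell these apart, and the variable that could help is kept in a separate tertiary outcome.

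A second, smaller matter is that baseline therapy is likely to be prognostic for 12-month HbA1c and is already recorded, yet the primary model does not use it.

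**Working it through.** **1. The plan's own figures** (Sample Size Calculation: difference 5, SD 11, 90% power, two-sided 5%, ICC 0.01, average group size 10, 15% loss).
- Normal approximation: n = 2 × (1.960 + 1.282)² × (11/5)² ≈ 101.7, so 102 per arm. The t-test version gives 102.7, so 103, which matches.
- Design effect: 1 + (10 − 1) × 0.01 = 1.09. Then 103 × 1.09 = 112.3, rounded to 120 in groups of 10.
- Loss: 120 / 0.85 = 141.2, rounded to 150 per arm. This matches.

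**2. Precision at 12 months.** Analysed per arm: 150 × 0.85 = 127.5. The design effect applies in the HEAL-D arm only, since controls are treated as groups of one.
- SE = 11 × √(1/127.5 + 1.09/127.5) = 1.41 mmol/mol.
- Power for 5 mmol/mol = Φ(5/1.408 − 1.96) = 94.4%.
- This takes the stated SD of 11 as the residual SD under the planned covariates, which the article does not specify.

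**3. How much of the difference could run through drugs.** Share = (between-arm difference in proportion intensified) × (HbA1c effect per intensification). Both inputs are assumptions, because the documents give neither.

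| Effect per intensification (mmol/mol) | 5 points | 10 points | 15 points | 20 points |
|---|---|---|---|---|
| 5 | 0.25 | 0.50 | 0.75 | 1.0 |
| 10 | 0.50 | 1.0 | 1.5 | 2.0 |
| 15 | 0.75 | 1.5 | 2.25 | 3.0 |

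If intensification is commoner in the control arm, a 5 mmol/mol behavioral effect would appear as 4.75 down to 2.0. Power to detect the net difference would be 92% at 4.75, 81% at 4.0, 57% at 3.0 and 29% at 2.0. If it is commoner in the HEAL-D arm, the same amounts would be the drug-related part of the observed difference. Drugs alone would produce the full 5 mmol/mol only with a gap of 5/15 = 33 points or 5/10 = 50 points.

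**4. Baseline therapy as a covariate.** Randomization balances it in expectation. For a therapy used by 20% to 50% of participants, the SE of a chance imbalance is √(2p(1 − p)/127.5) = 5.0 to 6.3 percentage points. The confidence interval already allows for this. The gain from adjusting is in precision only, with residual SD = 11 × √(1 − R²):
- R² = 0: SE 1.41, power 94.4%
- R² = 0.05: SE 1.37, power 95.4%
- R² = 0.10: SE 1.34, power 96.3%

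The R² values are assumed.

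**The case against.** The strongest reply is that nothing is wrong with the primary analysis. The aim is glycemic control in a pragmatic trial. Comparing HbA1c regardless of prescribing answers it, and drug changes that follow from allocation are part of the effect, not contamination. That stands. A reader might infer that free drug changes mean the HbA1c result cannot be read as a HEAL-D effect at all. The documents do not support this, since the effect of offering the program under usual care is exactly what is estimated. A reader might also infer bias from the omitted baseline covariate. Randomization rules that out.

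Four further points carry weight:
- The article says participants and researchers are unblinded. It does not say that prescribers know the allocation, so arm-dependent prescribing is possible but not established.
- Engagement with diabetes management can reasonably include attending medication review, so a drug-mediated gain does not flatly contradict the surrogate rationale.
- Self-management does not rest on HbA1c alone. Self-efficacy, dietary competence, knowledge, diet quality and physical activity are separate secondary outcomes.
- A mediation analysis is planned. Its mediators are not named, and the analysis plan, which is not shown, may name therapy.

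These points narrow the concern without removing it. The covariate set, the tertiary placement of drug change and the self-management reading of HbA1c are all fixed in the article, and no stated analysis joins them.

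**Conclusion.** This is an inexpensive improvement, not an error that invalidates the primary result. The 12-month comparison is a valid pragmatic effect on glycemic control. What the stated plan does not support is crediting that difference, on its own, to better self-management. On assumed inputs, 0.25 to 3.0 mmol/mol could run through prescribing in either direction. That is enough to matter for interpretation against a target of 5, but it would account for the whole target only with a very large prescribing gap. Leaving out baseline therapy costs precision alone, about 2 percentage points of power if it explains an assumed 10% of residual variance, in a trial that on the stated inputs already exceeds its 90% target.

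**What to change.** 1. Add baseline glucose-lowering therapy class (for example none; oral or non-insulin injectable; insulin) as a fixed effect in the primary model.
2. State that the primary effect is regardless of later therapy change, and do not adjust it for therapy after randomization. Such therapy may be on the causal path, and conditioning on it could introduce bias.
3. Report therapy change by arm beside the 12-month HbA1c result, and prespecify one supplementary analysis linking them. Naming therapy change as a mediator in the mediation analysis already planned is the natural choice. HbA1c at 6 months can both result from allocation and prompt a therapy change, so the analysis should say how it handles this. A composite ranking HbA1c improvement together with therapy change is optional, since its rules for net intensification would be open to dispute.
4. Limit self-management conclusions to what these analyses and the secondary self-efficacy, knowledge, diet and activity measures support.

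The cost is wording, one more covariate and one extra analysis on data already collected. The weakness is that the supplementary analysis relies on self-reported therapy. All of it can be settled before the primary analysis expected in July 2027.

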### Measurements

At baseline and all follow-up visits, unless specified otherwise, the following measurements will be conducted.

#### HbA_1c_ and Blood Lipids

A 5 mL venous blood sample (nonfasting) will be taken via venepuncture according to local standardized operating procedures for measurement of HbA_1c_ and full lipid profile by the pathology department at the corresponding clinical site. Biological samples taken for the study will be destroyed once analyzed in accordance with the Human Tissue Act 2004.

#### Blood Pressure

Brachial arterial blood pressure will be measured in the seated position using an automated sphygmomanometer after participants have been resting for ~5 minutes. Three blood pressure measurements will be obtained, and the average of the last two measurements will be used.

#### Anthropometry

Body weight will be measured using digital scales, with the patient wearing light clothing (without shoes), to the nearest 0.1 kg. Height will be measured to the nearest 0.5 cm, using a stadiometer, without shoes. Waist circumference will be measured using a flexible tape, with the patient wearing only light clothing, using the WHO methodology, which defines the “waist” as the midpoint between the lowest rib and the iliac crest. The mean of three waist circumference measurements will be recorded. Body composition will be measured using Tanita DC-430-MA P bioelectrical impedance scales; body fat (%) and lean mass (kg) will be recorded.

#### Physical Activity

Physical activity will be measured objectively, using a wrist-worn accelerometer over 7-10 days, measuring sleep, inactivity, step count, total physical activity, and moderate to vigorous physical activity. Accelerometer use will occur at baseline and the 12-month visits only. Self-reported physical activity will be recorded using the short International Physical Activity Questionnaire, which consists of seven questions about the amount of time spent in different levels of physical activity (vigorous, moderate, and low intensity), categorizing overall physical activity levels as low, moderate, or high [47].

#### Patient Reported Outcome Measures

Several patient-reported outcome measures, including diabetes-specific measures, will be collected:

QoL will be assessed using EQ-5D-5L [48] and used in the cost-effectiveness evaluation.Diabetes-related distress will be assessed using the 5-point Problem Areas in Diabetes (PAID-5) questionnaire [49]; PAID-5 is widely used in diabetes trials as an indicator of diabetes-specific QoL.Depressive symptoms will be assessed using the Patient Health Questionnaire-9 (PHQ-9) [50]; PHQ-9 is used widely, including in the NHS, to assess symptoms of depression.Diabetes knowledge will be assessed using the Short Diabetes Knowledge Instrument (SDKI) [51].Diabetes self-efficacy will be assessed using the Diabetes Management Self-Efficacy Scale [52].Diabetes dietary competence will be assessed using the Perceived Diabetes and Dietary Competence (PDDC) [53].Multimorbidity treatment burden will be assessed using the Multimorbidity Treatment Burden Questionnaire [54].The Diet Quality Questionnaire will be used to assess dietary adequacy, providing a measure of diet diversity and protection against noncommunicable diseases [55].Health service resource utilization will be assessed using an adapted Adult Service Use Schedule [56] and will be used to inform the health economic evaluation.Self-reported sleep duration and chronotype will each be assessed using an individual question adapted from the Morningness-Eveningness Questionnaire [57].

The EQ-5D-5L, PAID-5, PHQ-9, SDKI, DSMES-UK, and PDDC have evidenced reliability and validity for use in people with T2D [48-53]; none of the questionnaires have been validated specifically in populations of African and Caribbean heritage, although the SDKI and PDDC have been used in studies with African-American populations. The questionnaires will be interviewer-led or self-completed, depending on participant preference or literacy.

#### Internal Feasibility Assessment

A feasibility assessment will be conducted in the first 6 months of the trial to establish the feasibility of completing the trial within desired timelines, focused on (1) identification of eligible participants, (2) consent and randomization of eligible participants, and (3) engagement with treatment allocation of randomized participants. Recruitment and intervention engagement data will be reviewed by the Trial Steering Committee (TSC) with predefined “stop/go” criteria to determine progression to full trial.

#### Health Economic Evaluation

The primary aim of the health economic evaluation will be to assess the within-trial incremental cost-effectiveness of both remote and F2F versions of HEAL-D compared to standard DSMES programs. This will be undertaken through a cost-utility analysis with participant outcomes measured in quality-adjusted life years (QALYs) gained. Secondary aims include: (1) whether within-trial cost-effectiveness conclusions are affected by a consideration of long-term cost and QALY outcomes extrapolated from observed clinical end points within the clinical trial, and (2) whether the program is likely to be cost-effective when delivered at scale in routine practice, accounting for costs of implementation, such as facilitator training, and expected population reach or engagement levels.

Inferences regarding the cost-effectiveness of HEAL-D will be made with reference to the incremental cost-effectiveness ratio, applying varying cost-effectiveness thresholds (inclusive of those adopted by The National Institute for Health and Care Excellence) for identifying whether new health programs offer the NHS sufficient value for money [58]. The resource and cost implications of HEAL-D will be evaluated from an NHS or Personal Social Services perspective. All analyses will be undertaken probabilistically to reflect uncertainty in key economic and clinical parameters of relevance.

The short-term costs and benefits of HEAL-D will be quantified using data collected over the trial period, including resource inputs allocated to program delivery and implementation (eg, training activity), wider service utilization among trial participants over follow-up (using the self-report Adult Service Use Schedule), and short-term health-related QoL outcomes (based on the EQ-5D-5L instrument). For secondary analysis, long-term resource and QALY impacts will be estimated using the UKPDS Outcomes model [59]. The UKPDS is a microsimulation modeling tool that can be applied to make extrapolations regarding the incidence of complications (micro and macrovascular) and associated costs, QoL, and survival trajectories.

In further secondary analysis, we will draw on data and evidence from the main evaluation of program cost-effectiveness to assess whether it would be cost-effective to deliver alternative versions of HEAL-D at scale within routine service settings within a defined locality and population (South London). We will use existing frameworks and toolkits [60,61] to estimate the potential costs of implementation at scale and will evaluate the cost-effectiveness of scale-up, allowing for implementation costs and population engagement or reach.

#### Mixed Methods Process Evaluation

An embedded mixed methods process evaluation, combining relevant data gathered within the trial (questionnaires, monitoring data), qualitative interview data, logbook entries, workshops, and observations, will provide a formative evaluation of the intervention’s implementation, mechanisms of action, and identification of the contextual factors that influence its implementation and adoption. Implementation will encompass: fidelity (whether training and the intervention sessions were delivered as intended, whether healthcare professionals delivered culturally sensitive behavior change support, and any observed barriers to this), intervention dose (ie, attendance and completion rates), and reach (whether the intended audience encounters the intervention, and how). Mechanisms of action will encompass: satisfaction (with the program), participant and facilitator experience of the intervention, and effective and less effective components of the intervention in engaging participants and producing desired results (eg, increasing physical activity) and potential reasons. The identification of contextual factors that influence the implementation and adoption of HEAL-D includes implications for workforce capacity and for intervention integration within existing care.

Participants who are randomized to the HEAL-D intervention arm and staff involved in HEAL-D delivery will be eligible to participate in the process evaluation. We aim to recruit a total of 48 participants (16 per center) based on sampling for diversity in relation to high versus low intervention engagement, F2F versus remote attendance, and MLTC versus non-MLTC status. Maximum variation in sampling of participants will be guided by age, gender, employment status, and ethnicity (Black African or Black Caribbean). The characteristics of the sample will be continually reviewed to achieve balanced representation, inviting consecutive participants until the target sample and data saturation have been achieved. We aim to recruit up to 27 staff (9 per center), including delivery staff and trainers. Staff must meet the following criteria to participate: clinical and nonclinical staff working at or in partnership with centers participating in the HEAL-D trial, aged 18 years or older, and able to give written informed consent.

Data for the process evaluation will be collected via several means. First, both the training of HEAL-D facilitators and the delivery of HEAL-D sessions by facilitators will be observed. A self-report questionnaire, completed at the 12-month visit, will be used to assess the acceptability of trial procedures by participants. Participants will also be invited to undertake a semistructured interview within 1 month after the 12-month visit. These interviews will be conducted by telephone and provide an open and flexible method for exploring individual experiences in-depth. Participants and staff will also be invited to attend a F2F workshop to explore HEAL-D implementation.

